### Assignment of Interventions

#### Sequence Generation

Patients will be allocated to 1 of the 2 study groups based on a computed-generated blocked randomization, with stratification by 2 factors (type 2 diabetes mellitus and platelet hyperreactivity). For that purpose, randomly permuted blocks of sizes 4, 6, and 8 will be used in order to maintain the integrity of the randomization and blinding [24]. The software used to generate the sequence is available at randomization.com, and the study pharmacists will coordinate the randomization, treatment assignment, and delivery of study medication [25].

The research pharmacists will determine the study allocation and randomization and will be the only individuals to know the identity of the drugs delivered.

#### Blinding

The trial is triple-blinded to the treatment allocation: participants, study clinicians, and staff, as well as data analysts, will not know participant treatment assignments. Blinding will be assured by the use of a placebo comparator, which will be identical in look and taste to the active drug and will last until the data are analyzed.

A questionnaire will be used to assess the effectiveness of the participant’s blinding. This will be performed according to the methodology proposed by Rees and collaborators [26]. Every 2 weeks, participants will be asked to complete a survey about the intervention they think have received (active intervention, placebo, or unknown) and their level of certainty on a Likert scale. The accuracy of their answers will be evaluated using the Howard index, and differences in beliefs between 2 successive questionnaires will be assessed using the Fisher exact test. Participants’ beliefs about their treatment assignment are considered consistent if all responses are sequentially identical over time, except one change of opinion that may be explained by a lack of blinding [26].

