#### Sample Size

Sample size was calculated based on estimates for the rate of events in the primary composite outcome over 1 year: TIMI major bleeding (placebo 1% vs aspirin 2.5% [15]), cardiovascular events (placebo 3.0% vs aspirin 2.5% [10]), and fistula thrombosis (placebo 19% vs aspirin 8% [23]), for a total 1-year event rate of 23% in the placebo group and 13% in the aspirin group. A sample size of 318 patients (159 per arm) provides 80% power to detect a difference between groups of this magnitude (corresponding to an HR of 0.53) using a 2-sided log-rank test and alpha=.05 (Power Analysis and Sample Size Software version 14, NCSS LLC). The sample size for the trial was increased to 342 patients (171 per arm) to account for estimated attrition of 10%.

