#### Statistical Methods

Statistical analysis will be performed including all randomized patients according to their assigned treatment group (ie, intention-to-treat). The software used will be Stata 14 (StataCorp LLC). All testing will be 2-sided with statistical significance defined as *P*<.05. The primary composite outcome (first time-to-event of thrombotic events and TIMI major bleeding) will be analyzed with Kaplan-Meier curves and a log-rank test to detect difference between the groups. Cox proportional hazards regression may be used to adjust for relevant covariates, if appropriate (eg, for any unbalanced baseline characteristics that may occur by chance). Similarly, secondary outcomes will be analyzed with Kaplan-Meier curves and log-rank tests for all events. For the secondary objectives, interaction terms will be included in the Cox models above to test for interaction between treatment status and (1) the presence of type 2 diabetes and (2) platelet hyperreactivity. The proportion of patients with TIMI minor bleeding in each group will be compared with a chi-square test. If necessary, multiple imputation will be used for missing data.

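### The blinding check applies an independent-samples test (Fisher exact) to paired answers, so it cannot validly test whether participants' beliefs changed between questionnaires; a minor point, fixed in one sentence

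*Protocol article*

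**What the plan says.** The Blinding section of the protocol article sets up a repeated survey: "Every 2 weeks, participants will be asked to complete a survey about the intervention they think have received". There are three possible answers (active, placebo, unknown), plus a certainty rating.

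Three things are then done with the answers:

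- **Accuracy:** "The accuracy of their answers will be evaluated using the Howard index".
- **Change over time:** "differences in beliefs between 2 successive questionnaires will be assessed using the Fisher exact test".
- **Stability within a participant:** beliefs "are considered consistent if all responses are sequentially identical over time", with an allowance for one change of opinion.

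The section attributes the approach to a cited source and does not say which table the Fisher test is applied to. Statistical Methods sets the general rule ("All testing will be 2-sided with statistical significance defined as" P<.05). Sample Size gives 342 participants, 171 per arm.

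**The concern.** Each participant answers both of any two successive questionnaires. The two sets of answers are therefore linked person by person, and the protocol's own consistency rule relies on that link. Fisher's exact test assumes that the two groups being compared are independent. This is a named method that does not suit the data, so it is not a detail that a condensed article may leave to another document.

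What is at stake is how this one component is read. A participant's belief is likely to resemble the belief he or she gave shortly before. When answers are positively correlated, an unpaired comparison overstates the variance of the change and loses power, most of all for small steps between adjacent questionnaires. A non-significant P value could then be reported as evidence that beliefs were steady when the test had little chance of showing otherwise.

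**Working it through.** The document states no error rate, power or effect size for this check, so there is no figure to reproduce.

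**Inputs from the document.** Two-sided alpha 0.05 (Statistical Methods); 171 respondents (one arm) or 342 (both arms) (Sample Size).

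**Assumptions, not in the document.** The answer is reduced to binary (for example active versus other). The share answering active at the first questionnaire is p = 33% or 50%. The within-person correlation φ between successive answers is 0.5 to 0.9, where feasible for the shift. At p = 50% with no shift, the proportion repeating their answer is 1 − 2p(1−p)(1−φ), which is 75% at φ = 0.5 and 95% at φ = 0.9.

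**Reading 1: the two answer distributions are compared as if independent.**

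*Step 1, size of the test.* With no shift, the true variance of the change in proportion is 2p(1−p)(1−φ)/n. An unpaired test uses 2p(1−p)/n. The large-sample rejection rate is therefore 2[1 − Φ(1.96/√(1−φ))]:

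- φ = 0.5: 1.96/0.707 = 2.77, giving 0.6%
- φ = 0.7: 1.96/0.548 = 3.58, giving 0.03%
- φ = 0.8: 1.96/0.447 = 4.38, giving about 0.001%

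The nominal rate is 5%.

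*Step 2, power by simulation* (3000 runs per setting, Fisher on the margins against exact McNemar on the switchers, range over the assumed p and φ):

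| True shift | Fisher, n=171 | McNemar, n=171 | Fisher, n=342 | McNemar, n=342 |
|---|---|---|---|---|
| 0 points | 0-0.5% | 1.5-3.9% | 0-0.6% | 2.3-4.2% |
| 5 points | 0-6% | 21-83% | 2-16% | 42-99.8% |
| 10 points | 31-42% | 71-99.9% | 80-93% | 95-100% |
| 15 points | 87-93% | 97-100% | 99.7-100% | 100% |

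A separate simulation with its own assumed switching rates, over the same sample sizes, gave 0-0.2% rejection with no shift. For 5 points it gave about 0-5% for Fisher against 48-92% for McNemar. Fisher detected 10 points in 34% (n=171) to 87% (n=342) of runs, and 15 points in 90% or more. The two sets agree in direction and order of size. The upper Fisher values in the table (up to 16% at n=342) come from the least stable answers, φ = 0.5.

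*Step 3, a check by hand.* Suppose all switches go one way. Exact McNemar gives P = 2 × 0.5^k for k switchers: 0.0625 at k = 5 and 0.031 at k = 6, so 6 suffice at any sample size. Fisher on the margins first falls below 0.05 at 19 of 171 (19/171 = 11%), or at 26 to 27 of 342 (about 8%).

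**Reading 2: the test is run on the cross-table of first answer by second answer.** Fisher then tests whether the two answers are associated. Two examples with 170 participants:

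- Stable beliefs, rows [80, 5] and [5, 80]: 160 of 170 (94%) repeat their answer and switches balance. Fisher P is about 2×10⁻³⁵. McNemar, with 5 switches each way, gives P = 1.
- Large one-way shift, rows [51, 34] and [0, 85]: Fisher P is about 1.5×10⁻²⁰; McNemar P is about 1.2×10⁻¹⁰.

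Fisher is extreme in both cases, and more so when nothing has changed. It does not separate stability from drift.

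**The case against.** Much of the case on the other side stands.

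- **A reader might infer that the test would almost never detect a shift.** That is too broad. It holds for shifts of about 5 points or less when answers are strongly correlated. Shifts of 10 points are found in most runs at n=342, and shifts of 15 points in nearly nine runs in ten or more at either size.
- **A reader might infer that blinding will therefore look intact.** The document does not support this. Accuracy of guesses, which bears most directly on unblinding, is judged by the Howard index, and stability by a per-participant rule; neither uses Fisher. A drift in belief is also not unblinding in itself: both arms could move towards active without anyone guessing better than chance.
- **A reader might infer that the primary result depends on this check.** It does not. The primary analysis is a log-rank test, outcomes are adjudicated by a blinded team, and the questionnaire concerns participants' blinding only.
- **The table tested is not stated, and the cited methodology is not at hand.** On the cross-table reading the error runs the other way, towards significance. If the test compared the number of changers between arms, the groups would be independent and Fisher would be valid. But the sentence compares questionnaires, not arms, and neither natural reading of it gives a valid test of change.
- **The switching rates and the binary answer are assumptions.** They affect the size of the power loss, not the mismatch itself.

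**Conclusion.** The method as written is wrong for the data: an independent-samples test is named for paired answers. On the marginal reading it is far too conservative and has little power for steps of about 5 points or less, the range that gradual drift between adjacent questionnaires would tend to produce. On the cross-table reading it does not test change at all. Either way, its P value cannot support a statement that beliefs did or did not change.

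The mismatch rests on the document alone. The numerical size rests on assumed correlations, switching rates and a two-category answer. The consequence is confined to one component of a supportive check, so the severity is minor.

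**What to change.** Rewrite the one sentence in the Blinding section:

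- For successive questionnaires, use a paired test: exact McNemar if the answer is reduced to two categories, Stuart-Maxwell marginal homogeneity if active, placebo and unknown are kept.
- State the table tested, and report the cross-table of switches by arm.
- Keep Fisher only for independent groups, such as the two arms' guesses at one time point.

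The cost is a wording change, with no new data and no effect on sample size.

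While editing, reconcile the interval: the Blinding section has the questionnaire every 2 weeks, whereas Table 1 lists it in the column for every 30 days. This is a separate matter, but it determines which questionnaires count as successive.

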#### Emergency Unblinding

In exceptional circumstances, unblinding may happen if knowledge of the actual treatment is essential for further management of the patient. In case of severe adverse events, investigators will discuss unblinding within 24 hours with a medical advisor from the Data and Safety Monitoring Board who is not involved with the trial. Unblinding will take place by the research pharmacy immediately after the decision is made.

### Data Collection, Management Analysis, and Monitoring

#### Data Collection

We intend to minimize missing data by having monthly visits with patients. An adherence check will be done by counting returned tablets as previously stated.

Regarding data collection and storage, the study team will be trained to oversee all key aspects of the protocol: (1) methodology, forms, and tools that must be used for the collection, entry, monitoring, and editing of data; (2) appropriated methods to communicate among investigators and between investigators and participants; and (3) importance of reporting data as close to real time as possible during the course of the study.

#### Data Management

For quality control, patient records (source documents) will be stored at the site, and the original data will be shared with the DCC. It is the responsibility of the investigator to keep, maintain, and provide the documents audited by IRB, sponsor, National Institutes of Health, US Food and Drug Administration, or other local regulatory agencies when necessary.

After the collection of study data, patient identification will be encoded, and only the investigator will have access to this information, in accordance with the Good Clinical Practices and the Declaration of Helsinki regarding confidentiality [27].

The collected data will be entered electronically in a Research Electronic Data Capture management system. This database is a cloud-based system, and it will have a backup in a hard disk in the DCC. The dataset will be encrypted in order to guarantee data safety and confidentiality.

#### Statistical Methods

Statistical analysis will be performed including all randomized patients according to their assigned treatment group (ie, intention-to-treat). The software used will be Stata 14 (StataCorp LLC). All testing will be 2-sided with statistical significance defined as *P*<.05. The primary composite outcome (first time-to-event of thrombotic events and TIMI major bleeding) will be analyzed with Kaplan-Meier curves and a log-rank test to detect difference between the groups. Cox proportional hazards regression may be used to adjust for relevant covariates, if appropriate (eg, for any unbalanced baseline characteristics that may occur by chance). Similarly, secondary outcomes will be analyzed with Kaplan-Meier curves and log-rank tests for all events. For the secondary objectives, interaction terms will be included in the Cox models above to test for interaction between treatment status and (1) the presence of type 2 diabetes and (2) platelet hyperreactivity. The proportion of patients with TIMI minor bleeding in each group will be compared with a chi-square test. If necessary, multiple imputation will be used for missing data.

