## Methods

### Participants, Interventions, and Outcomes

#### Study Design

We will perform a phase 2 randomized, single-center, placebo-controlled, triple-blind, superiority clinical trial with 1:1 allocation to receive either 100 mg of aspirin per day or placebo by mouth for 12 months. Randomization will be stratified based on 2 baseline characteristics: (1) the presence versus absence of type 2 diabetes mellitus and (2) the presence versus absence of platelet hyperreactivity. The study will start following approval of the Institutional Review Board (IRB) and will follow the ethical principles of the Declaration of Helsinki of the World Medical Association. The study design is illustrated in Figure 1.

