### Strengths and Limitations

The main strength of the trial is its study design, which includes allocation concealment, randomization, and triple-blinding in order to reduce possible bias. In addition, stratification will balance 2 variables that are strongly associated with the outcome, type 2 diabetes mellitus and platelet hyperreactivity, and will allow us to explore whether patients with these characteristics differentially respond to aspirin therapy. Overall, the study protocol is feasible for both investigators and patients, as study enrollment and subsequent visits will take place during or following the patients’ standard hemodialysis sessions.

Potential limitations of the study protocol include the difficulty in interpreting a composite outcome. The use of a composite primary outcome is supported by the fact that major bleeding rates are very rare, requiring a large sample size and lengthy study duration that would render the trial unfeasible. We address this issue by adding efficacy outcomes related to thrombosis to major bleeding outcomes. In order to clarify interpretation of the primary composite outcome, they are individualized in the secondary analysis. Regarding the study population, peritoneal dialysis patients will not be included as most do not have arteriovenous fistula and, hence, are not at risk for fistula thrombosis. Furthermore, glomerular disease patients who developed ESRD will not be included, as they show a different pattern of morbidity and mortality [20]. Another limitation is the possibility that we do not meet the planned recruitment time, as it will affect study power and validity. For that matter, we allow 12 more weeks for recruitment than initially planned. Last, despite the simplicity of drug administration, adherence is always a potential problem, which will be dealt with by identification of nonadherent patients and systematic training.

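### Randomization is stratified by two factors said to be strongly prognostic, but the primary log-rank test as written does not use them, and the only covariate criterion illustrated is chance imbalance

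*Protocol article*

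**What the plan says.** Protocol article, Study Design: "Randomization will be stratified based on 2 baseline characteristics". Sequence Generation repeats this for the allocation list, "with stratification by 2 factors (type 2 diabetes mellitus and platelet hyperreactivity", using permuted blocks of 4, 6 and 8.

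Strengths and Limitations gives the reason: "stratification will balance 2 variables that are strongly associated with the outcome, type 2 diabetes mellitus and platelet hyperreactivity". No hazard ratio or event rate by stratum is given anywhere in the article.

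Statistical Methods says that the primary composite "will be analyzed with Kaplan-Meier curves and a log-rank test to detect difference between the groups". The Sample Size section likewise sizes the trial "using a 2-sided log-rank test and alpha=.05". Neither sentence mentions the strata.

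Statistical Methods then allows Cox regression, as an option, to "adjust for relevant covariates, if appropriate (eg, for any unbalanced baseline characteristics that may occur by chance". The stratification factors appear in the analysis in one place only, the secondary objectives, where "interaction terms will be included in the Cox models above to test for interaction between treatment status" and each factor.

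**The concern.** Stratified allocation removes the between-arm variation due to the strata. A log-rank test that ignores the strata still counts that variation as noise, so when the strata are prognostic it rejects less often than its nominal level and gives up some power. The article says the strata are strongly prognostic and then, as written, does not use them in the primary test.

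The covariate sentence adds to this. What makes a covariate worth adjusting for is how well it predicts the outcome, not whether it happened to fall unevenly between arms. Stratified blocks tend to balance diabetes and hyperreactivity, so a trigger based on imbalance would tend to pass over the two variables the article considers most prognostic. The adjusted hazard ratio would also depend on which characteristics happened to look uneven. The secondary interaction tests are built on these same optional models.

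At stake are a small amount of power and a clearly defined adjusted estimate.

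**Working it through.** **1. The plan's own figure.** Inputs from Sample Size: 23% versus 13% at one year, hazard ratio 0.53, 80% power, 2-sided alpha .05, N = 318. The 12-month horizon is from Outcomes.

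- Hazard ratio = ln(1 − 0.13) / ln(1 − 0.23) = 0.533, which matches the stated 0.53.
- Events (Schoenfeld) = 4(1.960 + 0.842)² / (ln 0.533)², rounded up to 80. Mean event probability = (0.23 + 0.13)/2 = 0.18. N = 80/0.18 = 444.4, or 446 in two equal arms.
- Events (Freedman) = (1.960 + 0.842)² × [(1 + 0.533)/(1 − 0.533)]², rounded up to 85. N = 85/0.18 = 472.2, or 474 in equal arms.
- At N = 318, expected events are 318 × 0.18 = 57.2. Power = Φ(√57.2 × 0.629/2 − 1.960) = Φ(0.42), about 66% (Freedman 64%).

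So 318 is not reproduced on a 12-month horizon. A nearby figure, 314, appears with 12 months of uniform accrual and a common close at 24 months, which counts events beyond each patient's first 12 months. That is a separate matter. It is shown because it sets the starting power for the comparison below at about 65%.

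**2. Unstratified versus stratified log-rank.** Simulation with N = 318, 1:1 permuted blocks of 4, 6 and 8 within four equal strata, exponential times censored at 12 months, and marginal rates held at 23% and 13%. There were 15,000 null runs and 10,000 alternative runs per row. The factor hazard ratios are assumptions.

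| HR of each factor | Type I error, unstratified | Type I error, stratified | Power, unstratified | Power, stratified | Gain (points) |
|---|---|---|---|---|---|
| 1.0 | 4.8% | 4.8% | 64.6% | 64.4% | −0.2 |
| 1.5 | 4.7% | 4.9% | 65.8% | 66.4% | 0.6 |
| 2.0 | 4.5% | 5.2% | 64.9% | 66.6% | 1.7 |
| 3.0 | 3.6% | 4.9% | 65.9% | 70.2% | 4.3 |

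The Monte Carlo standard error is √(0.65 × 0.35/10,000), about 0.5 points, for each power figure, and √(0.05 × 0.95/15,000), about 0.2 points, for each error rate. The first two gains are therefore close to nil.

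Sensitivity: across four splits of the strata, equal and unequal (8,000 runs each), the gain was 0.4 to 0.6 points at HR 1.5, 1.3 to 1.8 at HR 2, and 3.3 to 4.6 at HR 3. With 446 patients and equal strata, power was 80.1% unstratified and 81.3% stratified at HR 2, and 80.5% and 83.6% at HR 3.

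**3. What an imbalance trigger would select.** Within a stratum, an unfinished block of 8 can leave the arms at most 4 patients apart. Each level of a factor spans two strata, so the arms differ by at most 8 patients at any level, out of 342. The trigger is unlikely to pick the stratification factors.

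For other covariates, assume eight candidates, each selected if its between-arm difference has |z| > 1.645 (a 10% chance each). The chance that at least one is selected is 1 − 0.9⁸ = 57% if they are independent, so the content of the adjusted model would often be settled by chance. In 4,000 null runs at each of three assumed prognostic strengths, the selected Cox model rejected in 3.7% to 4.8%. Taking the better of the unadjusted and selected results gave 4.8% to 5.5% (standard error about 0.35 points).

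**The case against.** Four points can fairly be made against this.

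- **Nothing says the test is unstratified.** The article says only that a log-rank test will be used, and an analysis plan that is not shown could stratify it. Sizing a trial on a plain log-rank test is normal even when the analysis will be stratified. This stands: the absence of stratification is read from the plain wording and is not a stated decision. It is still the only specification given, and it sits beside an explicit claim of strong prognosis.
- **Imbalance is introduced as an example, for a model that is itself optional.** This stands. A reader might infer that chance imbalance is the sole criterion for adjustment, but the text also speaks of relevance and does not exclude prognostic covariates. What remains is that the one example given is a poor guide.
- **Data-dependent adjustment does little measured harm to error rates.** This also stands. Under Blinding, data analysts do not know the assignments, which limits choosing covariates to favour one arm. Coded groups would still show imbalance, so the adjusted estimate remains unfixed.
- **The strata do enter the analysis.** They do, through the interaction models, which would ordinarily include both main effects. Those models serve the secondary objectives and do not alter the primary test.

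**Conclusion.** The point holds as a modest improvement to the plan. As written, the primary test does not use the randomization strata. It remains valid. A reader might infer that an unstratified test after stratified randomization inflates false positives, but the simulations show the opposite: type I error of 3.6% to 4.8%. Nor can any later choice of Cox covariates alter the named log-rank test.

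The cost is about 0 to 2 points of power if each factor has a hazard ratio of 1 to 2, and about 4 points at 3, which implies a ninefold hazard range (3 × 3) between extreme strata. These multipliers are assumptions. A reader might also infer that stratifying would repair the trial's power. It would not: at N = 318 with 12 months per patient, stratified power is still only about 64% to 70% over this range.

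The imbalance example is a poor criterion because it looks away from the prognostic factors and leaves the adjusted hazard ratio to the observed data. The objection is to an unfixed estimate, not to material error inflation.

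**What to change.** In Statistical Methods:

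- Make the primary test a log-rank test stratified by type 2 diabetes and platelet hyperreactivity, using the values recorded at randomization. The article re-measures hyperreactivity at later visits, so the text should say that the baseline value is meant.
- Estimate the hazard ratio from a Cox model stratified by the same two factors.
- Replace the imbalance example with a short list of covariates chosen on prognostic grounds and fixed before unblinding, or state that there are none.

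The cost is two or three sentences. Both factors are already collected for randomization. If they prove unrelated to the outcome, stratifying costs essentially nothing (64.4% against 64.6% power in the simulation). According to the Results section, the trial has yet to be submitted for ethical review and registered, so the change can be made before enrollment.
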